### **2.4 Methodology**

#### **2.4.1 Trial Design**

This is a 15-site, two-arm, randomized controlled trial, which will be performed from Oct 1, 2012 to Nov 30, 2014 (Figure 1). All the acupuncturists in each site are required to have an official license and clinical work experience no less than 2 years. In this trial, the participants, evaluators, and statisticians will be blinded.

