#### 2.4.5 Randomization

Participants will be randomized to EA and SA groups with a ratio of 1:1 by using the central stratified block randomization. The site will be set as the stratified factor. The professional biostatisticians will

generate the randomization schedule and related document by using SAS 9.3 software, PROC PLAN. A central randomization system (Institute of Basic Research in Clinical Medicine, China Academy of Chinese Medical Sciences) will be adopted. The researchers who take charge of the randomization will input the birthdate and gender of the eligible subjects through telephone or website to get the random numbers. Experts who will generate the randomization schedule from the Institute of Basic Research in Clinical Medicine, China Academy of Chinese Medical Sciences will take no part in the statistical analysis. The randomization schedule and the related parameters will be sealed and signed by the experts and kept by the staff that doesn't participate in our research. No one has the right to check the randomization schedule.

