As the main objective is to compare the changed number of weekly average CSBMs throughout the 8 weeks of treatment with the average weekly CSBMs during the 2 weeks baseline period, the primary analysis of the patient-level data is the number of CSBMs per week for 8 weeks. It means the total amount of CSBMs during 8 weeks will be divided by eight to achieve the result. (Each patient therefore has one number of weekly CSBMs throughout the 8 weeks of treatment). The null hypothesis is this number of CSBMs is the same between the EA and SA groups, and the alternative hypothesis is that the change from baseline in CSBMs at 8 weeks for the EA group does not equal the SA group. The subjects who do not receive any treatment after randomization or receive treatment but not any efficacy assessment data are classed as missing data, and multiple imputation methods will be used to deal with the missing data. An analysis of covariance (ANCOVA) will be used group, study site and baseline CSBMs will be included in the ANCOVA model. The secondary outcome measures include the following seven items: 1) the proportion of participants with three or more mean weekly CSBMs during weeks 1–8 and weeks 9–20; 2) the change from baseline in mean weekly CSBMs during weeks 9–20; 3) the change from baseline in mean weekly spontaneous bowel movements (SBMs); 4) the change from baseline in mean stool consistency over weeks 1–8; 5) the change from baseline in mean straining scores over weeks 1–8; 6) the change from baseline in PAC-QOL scores at week 8; 7) the proportion and mean weekly frequency of rescue medicine and other defecation assistances used. Chi-square test was used to compare the proportion of participants having three or more CSBMs and the proportion of other rescue medicine and other defecation assistances used between two groups. Student's t test was used to compare the change from baseline of mean weekly SBMs and the scores in PAC-QOL, stool consistency, and straining between groups. Wilcoxon rank sum test was used to compare the mean weekly frequency of other rescue medicine and other defecation assistances used between groups. Subgroup analysis will be conducted according to the subject's age (<65 years and ≥65 years). All adverse events and serious adverse events will be listed. Poisson regression model will be used to compare the incidence of adverse events between the EA and SA groups.

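### Secondary change scores and responder proportions are compared without the site and baseline adjustment used for the primary endpoint, so their precision is lower than attainable

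*Protocol*

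**What the plan says.** For the primary endpoint, Protocol 8.3 states: "An analysis of covariance (ANCOVA) will be used group, study site and baseline CSBMs will be included in the ANCOVA model".

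The same section then names simpler tests for the secondary endpoints:

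- Continuous endpoints: "Student's t test was used to compare the change from baseline of mean weekly SBMs and the scores in PAC-QOL, stool consistency, and straining".
- Responder endpoints (weeks 1–8 and weeks 9–20): "Chi-square test was used to compare the proportion of participants having three or more CSBMs".
- Rescue and assistance frequency: "Wilcoxon rank sum test was used to compare the mean weekly frequency of other rescue medicine and other defecation assistances used between groups".

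No covariate or stratum is mentioned for any of these. One listed secondary outcome, "2) the change from baseline in mean weekly CSBMs during weeks 9–20", is given no test at all, although section 2.3 makes the sustained effect something to be evaluated.

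On the design, 2.4.1 says "This is a 15-site, two-arm, randomized controlled trial", and 2.4.5 says of the randomisation: "The site will be set as the stratified factor". Section 2.4.7.2 defines the t-tested endpoints as changes from baseline. Stool consistency and straining are averages per SBM, with the SBM count of the two baseline weeks as the baseline divisor.

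**The concern.** The plan judges site and baseline worth adjusting for in the primary analysis, then drops both for the secondary endpoints without giving a reason.

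- **Baseline.** Subtracting the baseline fixes its slope at 1. If the true slope of follow-up on baseline is b, a chance baseline difference d between the arms leaves (b − 1)d in the estimated effect. ANCOVA estimates the slope and removes that residual.
- **Site.** Stratified randomisation balances the arms within site. An analysis that ignores site leaves between-site variation in the error term, so the standard error is a little too wide.

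What is at stake is the precision of the symptom, quality-of-life and responder results. For a modest true effect, this could decide whether a secondary comparison reaches significance.

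**Working it through.** **The plan's own figure.** The protocol gives no precision or power for any secondary endpoint. Its only figure is the 1034 in 2.4.4, for the primary endpoint. The inputs there are SDs 1.77 and 1.61, 95% power, two-sided 5% and 20% loss. The pooled SD is √((1.77² + 1.61²)/2) = 1.692. At the pilot difference of 1.49 − 1.01 = 0.48, n per arm = 2(1.960 + 1.645)² × 1.692²/0.48² = 323. That is 646 evaluable, or 646/0.8 = 808 enrolled. At 0.50 it is 596, or 745 enrolled. So 1034 is not reproduced, but it exceeds what the inputs require, and this has no bearing on the present point. It serves here only as planned enrolment: 1034 × 0.8 = 827 evaluable.

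**1. Baseline adjustment.** Let ρ be the baseline to follow-up correlation and k the baseline SD divided by the follow-up SD. Neither is in the protocol. In units of the follow-up variance:

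- change score: 1 + k² − 2kρ
- ANCOVA: 1 − ρ²
- difference: (k − ρ)², which is never negative

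So in large samples ANCOVA is never less precise. The gain vanishes when k = ρ. With k = 1 the variance ratio reduces to (1 + ρ)/2.

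| ρ (assumed) | k = 1: ratio | reduction | k = 0.5: ratio | reduction |
|---|---|---|---|---|
| 0.3 | 0.65 | 35% | 0.91/0.95 = 0.96 | 4% |
| 0.5 | 0.75 | 25% | 0.75/0.75 = 1.00 | 0% |
| 0.7 | 0.85 | 15% | 0.51/0.55 = 0.93 | 7% |

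At k = 1, the 1034 patients analysed by t test carry the information of 1034 × 0.65 = 672, 1034 × 0.75 = 776 and 1034 × 0.85 = 879 patients under ANCOVA.

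**2. Week 9–20 CSBM change.** Everyone enters with at most 2 CSBMs per week, so the baseline spread is limited. The variance saved is (1 − b)² × Var(baseline). Assume a uniform baseline over 0 to 2 (variance 4/12 = 0.33) and a change variance of 1.692² = 2.86. The saving is 0.33/2.86, about 12%, at b = 0, and 0.25 × 0.33/2.86, about 3%, at b = 0.5. For b between 0 and 1, it is at most about 12%.

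**3. Site.** Adjustment multiplies the standard error by about √(1 − ICC). This gives 0.990 at an ICC of 0.02, 0.975 at 0.05 and 0.949 at 0.10 (ICC assumed). Fourteen site parameters cost almost nothing against 827 patients.

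**4. Practical size (k = 1, N = 827).** If a secondary endpoint had the primary's change SD of 1.692 (assumption), the 95% half-width by t test would be 1.96 × 1.692 × √(4/827) = 0.231. Multiplying by √0.65, √0.75 and √0.85 gives 0.186, 0.200 and 0.213 by ANCOVA. The smallest difference detectable with 80% power, in follow-up SD units, is:

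| ρ | t test | ANCOVA |
|---|---|---|
| 0.3 | 0.231 | 0.186 |
| 0.5 | 0.195 | 0.169 |
| 0.7 | 0.151 | 0.139 |

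**5. Simulation.** The settings were 15 site strata, 1:1 within site, N = 828 and 1500 runs each. The t test's type I error was 3.6% to 5.3%. With a true difference of 0.2 SD and ICC 0.05, power by t test and by ANCOVA was 67% and 87% (ρ = 0.3), 83% and 93% (0.5), and 96% and 99% (0.7).

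**6. Responder proportions.** The formulas above do not apply to chi-square, and the protocol gives no responder rates, so no figure is offered.

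**The case against.** The strongest reply is that nothing here is wrong. Under 1:1 randomisation, a t test on change scores and a chi-square test are valid comparisons, and ignoring site is at worst slightly conservative. A simpler test for secondary than for primary endpoints is not a contradiction. All of that stands. A reader might infer invalid tests or inflated error from the mismatch, and the documents do not support that.

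A reader might also infer that precision is poor. That is not supported either. With 827 evaluable patients, even the t test detects about 0.15 to 0.23 SD with 80% power in the equal-SD case. Baseline is already subtracted, so only the (b − 1)d residual of an imbalance remains.

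The 15 to 35% reduction is one scenario, and with a smaller baseline SD it nearly disappears. For stool consistency and straining the opposite may hold. Their baseline mean rests on two weeks of SBMs against eight on treatment, so k could exceed 1 and the gain could be larger. The protocol settles neither case.

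The missing week 9–20 test may be supplied by a SAP, since 7.8 requires an approved one before database lock. It therefore supports the point but does not carry it.

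The objection does not show any advantage of the unadjusted tests. The change-score and responder tests are fixed in the protocol itself, and in large samples ANCOVA is never less precise than the change-score t test.

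**Conclusion.** The point holds as one of efficiency and consistency, not validity. For SBMs, PAC-QOL, stool consistency, straining and the proportions with three or more CSBMs per week, 8.3 leaves out the stratification factor and the baseline covariate that its own primary model uses.

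The size is a range resting on assumptions:

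- a variance reduction of 35% to 15% for ρ from 0.3 to 0.7 with equal SDs;
- 0 to 7% over the same ρ if the baseline SD is half the follow-up SD;
- about 1 to 5% in standard error from site at an ICC of 0.02 to 0.10;
- unquantified for the responder proportions, where the restricted baseline probably limits what adjusting for baseline CSBMs could add.

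Two limits apply. Rescue and assistance frequency, compared by Wilcoxon, is outside the point. Patients with no SBM in the two baseline weeks have no stool or straining baseline, so the change score and ANCOVA are equally undefined for them. The primary analysis is untouched. The change is worth making because it is free, not because a conclusion is known to be at risk.

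**What to change.** Reword the secondary analyses in 8.3:

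- **Continuous secondaries** (SBMs, PAC-QOL, stool consistency, straining and the week 9–20 CSBM change): ANCOVA with group, site and the endpoint's own baseline, reporting the adjusted difference with its 95% confidence interval.
- **Proportions with three or more CSBMs per week** (weeks 1–8 and 9–20): a Mantel-Haenszel analysis stratified by site, reporting the risk difference with its confidence interval. With 827/15, about 55 evaluable patients per site on average, the strata are generally large enough.
- **Sensitivity analyses:** keep the t test and chi-square test.
- **Stool and straining:** state how patients with zero baseline SBMs are handled. This is needed under either method.

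The cost is wording only. Site and the baseline diary and PAC-QOL values are already collected, so no new data or visits are needed. The change should be made before unblinded data are examined.

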### **3.3 Safety related to EA**

Adverse events will be recorded and measured both by participants themselves and acupuncturists. Acupuncturists are responsible for the recording of the EA-related adverse events on the CRF. The adverse events relating to acupuncture include broken needle, needle left in the body after treatment, nausea during acupuncture, fainting caused by needling during the treatment, pricking lasted more than half an hour (no matter how much the intensity is) after acupuncture, hematoma or bleeding around the site of needling, numbness or infection around the site of needling, sleeplessness after acupuncture, dizziness after acupuncture, other discomforts (including palpitation, headache, anisotopia, drowsiness, or aggravation of existing symptoms) after acupuncture. Acupuncturists will record the symptoms, frequency, degree, and the duration of each AE. The pricking caused by needling will be assessed through 10-point visual analog scale (VAS). We will compare the proportion of participants who get acupuncture-related adverse effects, and the frequency of occurrence of each adverse effect between EA and SA groups. Participants who get acupuncture-related adverse effects at least once will be counted in for the comparison of the proportion.

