#### **4.1 Electro-acupuncture (EA)**

Acupoints:

Bilateral Tianshu (ST 25), Fujie (SP 14), Shangjuxu (ST 37).

Location:

According to the WHO Standardized Acupuncture Points Location.

Manipulation:

After sterilizing the skin in participants with supine position, needles of the size of 0.30 mm×50 mm, or 0.35 mm×75 mm will be inserted into ST25 and SP14 slowly and vertically, without manipulation, for approximately 30 to 70 mm until they pierced the muscle layer of the abdominal wall. Paired alligator clips of the EA apparatus will be attached transversely to the needle holders of the bilateral ST25 and SP14. EA stimulation will last for 30 minutes with a dilatational wave of 10/50Hz and current intensity of 0.1 to 1 mA. The skin around the acupoints shivering mildly indicates the proper dose. Needles of the size of 0.30 mm×40 mm will be inserted into ST37 vertically for about 25 to 30 mm. Three small equal manipulations of twirling, lifting and thrusting will be performed. The participants' feeling of sore and distention show the proper manipulation. The manipulation on ST37 mentioned above should be performed every 10 minutes, three times in 30 minutes.

Course of treatment:

Each participant will accept an 8-continuous-week treatment with 28 sessions in total. The participants will be treated 30 minutes once, once a day, five times per week in the first two weeks, and three times per week in the latter 6 weeks.

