#### **8.3 Statistical Contents and Methods**

All statistical analyses will be two-sided tests. For all statistical analyses, SAS 9.4 software will be used. A P value of less than 0.05 ( $\alpha$ -value of 0.05) is considered to indicate statistical significance.

Analysis of baseline characteristics will analyze the demographic data and other baseline measures. Mean and standard deviation will be used in the continuous variables and percentages in the categorical variables. For comparisons the two independent sample, t-test will be used for continuous variables and Chi-squared test for categorical variables. Non-parametric tests may also be used. A Fisher Exact test will be used to describe the case distribution in the EA group and the SA group and to calculate the total dropout rate and the dropout rate caused by adverse events between the two groups. A Chi-square test is used to analyze the difference in compliance between the two groups to evaluate if the participants in the EA group and the SA group receive the specified treatment according to the protocol.

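### The Poisson model for adverse events is not tied to an outcome or a variance; with default standard errors it would be over-precise for clustered repeat events and over-cautious for the proportion with any event

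*Protocol*

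**What the plan says.** Section 8.3 states that "Poisson regression model will be used to compare the incidence of adverse events between the EA and SA groups". It names no outcome coding, variance estimator, dispersion term or exposure offset. The same section says "All statistical analyses will be two-sided tests" and sets the 0.05 significance level for all analyses.

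Section 3.3 describes two between-group comparisons of acupuncture-related events. One is the proportion of participants affected: "Participants who get acupuncture-related adverse effects at least once will be counted in for the comparison of the proportion". The other is "the frequency of occurrence of each adverse effect between EA and SA groups". The data for the second will exist, because "Acupuncturists will record the symptoms, frequency, degree, and the duration of each AE". Neither comparison is given a method.

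On exposure, section 4.1 says "Each participant will accept an 8-continuous-week treatment with 28 sessions in total", and section 4.2 gives the sham group the same course.

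**The concern.** Incidence in section 8.3 can mean either comparison in section 3.3, and a Poisson model with its default variance suits neither.

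- **Event counts.** Haematoma, prolonged pricking or dizziness can recur in the same person over 28 sessions. If some participants are more prone than others, the variance of the count exceeds its mean. The default Poisson standard error is then too small, and false safety signals become more likely.
- **At least one event.** The variance of a 0/1 outcome is p(1 − p), which is below its mean p. The default Poisson standard error is then too large, and a real difference is somewhat harder to see.

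The two errors run in opposite directions, so while the outcome is unnamed even the direction is unknown. Section 8.3 already makes this distinction for rescue medicine, where the proportion gets a chi-square test and the weekly frequency a rank sum test. Adverse events have the same two-part structure but only one model.

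Safety is part of the study objective (sections 2.1 and 2.3). The arms differ in needle depth (30 to 70 mm against 3 to 5 mm) and in whether current flows, so this comparison will be read closely.

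**Working it through.** **Inputs from the protocol.** Two-sided alpha 0.05 (8.3); 28 sessions per participant in both arms (4.1, 4.2); 1034 participants at 1:1, so 1034 / 2 = 517 per arm (2.4.4, 2.4.5).

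**Assumed.** Event rates, the variance-to-mean ratio φ and the within-person correlation ρ. The protocol states none of these, and it gives no safety power or precision figure to reproduce.

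**Step 1: counts.** With variance φ times the mean, the default Poisson standard error of the log rate ratio is 1/√φ of the true one. True error = 2[1 − Φ(1.96/√φ)].

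| φ (assumed) | Default SE / true SE | True two-sided error |
|---|---|---|
| 1.0 | 1.000 | 5.0% |
| 1.2 | 0.913 | 7.4% |
| 1.5 | 0.816 | 11.0% |
| 2 | 0.707 | 16.6% |
| 3 | 0.577 | 25.8% |

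**Step 2: at least one event.** With risk p, the default Poisson standard error of the log risk ratio is 1/√(1 − p) times the true one. True error = 2[1 − Φ(1.96/√(1 − p))].

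| p (assumed) | Default SE / true SE | True two-sided error |
|---|---|---|
| 1% | 1.005 | 4.9% |
| 5% | 1.026 | 4.4% |
| 10% | 1.054 | 3.9% |
| 20% | 1.118 | 2.8% |
| 30% | 1.195 | 1.9% |

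**Step 3: how much clustering produces such a φ?** For beta-binomial events with per-session risk m, φ = (1 − m)(1 + 27ρ). At m = 0.005, ρ = 0.01 gives 0.995 × 1.27 = 1.26, and ρ = 0.05 gives 0.995 × 2.35 = 2.34. Over 28 sessions a small correlation is enough.

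**Step 4: simulation under no group difference.** 517 per arm, 28 sessions, 4000 replicates, m = 0.002, 0.005 and 0.02. The ranges run over the three values of m.

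| ρ (assumed) | Count, default variance | Count, robust variance | Any event, default variance | Any event, robust variance |
|---|---|---|---|---|
| 0.01 | 7.7% to 8.3% | 4.9% to 5.6% | 1.2% to 4.7% | 4.5% to 5.4% |
| 0.05 | 18.7% to 21.0% | 4.9% to 6.1% | 1.9% to 4.4% | 4.5% to 5.1% |
| 0.10 | 30.0% to 30.4% | 5.3% to 7.0% | 2.9% to 4.4% | 4.4% to 5.1% |
| 0.20 | 42.5% to 43.9% | 5.8% to 9.4% | 3.6% to 3.9% | 3.9% to 5.2% |

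Robust variance, taken at participant level, brings both outcomes close to 5% in most settings. The exception is counts that are very rare and strongly clustered. At m = 0.002 the robust test has an error of 7.0% at ρ = 0.10 and 9.4% at ρ = 0.20. In the latter case only about 1.7% of participants, or 0.017 × 517 ≈ 9 per arm, have any event.

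**The case against.** A reader might infer that the protocol commits to an unadjusted Poisson analysis and that its standard errors will therefore be wrong for both comparisons. The text does not support that. It names a model family and neither specifies nor excludes a robust variance, a scale term or an offset. Poisson regression with robust variance would satisfy the sentence and be valid for either outcome. Such details are often left to a statistical analysis plan, which sections 7.7 and 7.8 expect and which is not shown.

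Nor does the protocol say that the Poisson model serves the comparisons in section 3.3. That section concerns acupuncture-related events, while section 8.3 speaks of adverse events in general. Overdispersion is also not a stated fact: 28 sessions make repeats possible, but no rate or clustering is given. At φ = 1 there is no error for counts, and for 0/1 outcomes at risks up to 5% the error is negligible.

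Finally, no decision rule depends on this p-value. Adverse events are to be listed in any case, serious events are reported within 24 hours (3.2), and the monitoring board reviews both.

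All of this stands, and it limits the size and certainty of the point. It does not remove the mismatch between the single undefined incidence in section 8.3 and the two comparisons in section 3.3. It also does not remove the exposure to a default variance if the sentence is implemented as it reads.

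**Conclusion.** The point holds in conditional form. Section 8.3 fixes a Poisson model without saying which of the two comparisons in section 3.3 it serves. If the default model-based variance is used, the true error for counts is about 7% to 26% at assumed variance-to-mean ratios of 1.2 to 3. For the 0/1 outcome the standard error is under 3% too wide at risks up to 5%, and about 5% to 20% too wide at assumed risks of 10% to 30%. The count problem is the larger one and needs only modest clustering, but it disappears if events are independent.

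The formulas are standard. The rates, dispersions and correlations are assumptions. The change is worth making because it protects the safety comparison under either reading. The primary efficacy result does not depend on it.

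**What to change.** In section 8.3, assign a method to each comparison in section 3.3, and say whether the same methods apply to all adverse events or only to acupuncture-related ones.

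- **Event counts:** Poisson regression with participant-level robust variance, or negative binomial regression, with the log of sessions received or of time observed as offset. Anyone who received no session has no log-sessions value, so time observed is the simpler choice if all randomised participants are kept.
- **At least one event:** a risk difference or risk ratio with robust or exact confidence intervals.

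The cost is a sentence or two and a standard procedure in software already named. No new data are needed: section 3.3 already records event frequency, and the compliance rate in section 6.3 already needs the number of treatments received. The one downside is small: robust variance can stay mildly anti-conservative when events are very rare and strongly clustered. Such event types are better reported mainly as numbers of participants affected, with exact intervals.
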